#### 2) Immunogenicity Indicators

The positive rates of vaccine-related humoral and cellular immune responses observed in

subjects.

### **6.10.2 Sample Size**

In accordance with the clinical trial approval requirements of the China Food and Drug Administration, this Phase Ib study will enroll 36 healthy volunteers to receive the DNA-rTV vaccine.

### **6.10.3 Randomization**

To avoid subjective selection bias by researchers and severe imbalance in sample allocation, a block randomization method will be employed in this trial. The random number table for randomization will be generated by statisticians from the Health Statistics Office of the Chinese Center for Disease Control and Prevention using SAS 9.1.2 software.

The 36 participants will be divided into two phases based on the order of enrollment, with 18 participants in each phase. In the first phase, participants will be randomized in a 2:1 ratio to either the low-dose combined immunization group or the placebo group. In the second phase, participants will be randomized in a 2:1 ratio to either the high-dose combined immunization group or the DNA-only group.

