### 6.4.2 Immunization and Follow-Up Plan

The Phase Ib clinical trial requires a total of 36 volunteers, including those who have and have not previously received the smallpox vaccine. These volunteers will be divided into three groups: a combined immunization group (24 individuals) receiving three doses of the DNA vaccine and one dose of the rTV vaccine, a DNA-only group (6 individuals) receiving three doses of the DNA vaccine alone, and a placebo group (6 individuals) receiving only a placebo. The combined immunization group is further divided into a low-dose and a high-dose subgroup, each consisting of 12 individuals. Recruitment will aim to include an equal number of individuals who have and have not received the smallpox vaccine in each

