dose subgroup. Enrollment and vaccination will begin with the low-dose subgroup of the combined immunization group in the order of enrollment. The safety of the vaccine will be assessed within two weeks after each DNA vaccination in the low-dose subgroup. If no more than two vaccine-related adverse events of grade  $\geq 3$  (excluding fever above 39°C for no more than 3 days) occur, the trial will continue; if three or more such adverse events occur, subsequent vaccinations will be halted. Participants in both dose subgroups of the combined immunization group and the DNA-only group will receive three doses of 2 mg (low-dose subgroup) or 4 mg (high-dose subgroup) of the DNA vaccine at 4-week intervals. Enrollment and vaccination for the DNA-only group will commence simultaneously with the high-dose subgroup of the combined immunization group. If no more than two vaccine-related adverse events of grade  $\geq 3$  occur after each 4 mg DNA vaccination in the high-dose subgroup and the DNA-only group, the trial will continue; if three or more such adverse events occur, subsequent vaccinations in that dose subgroup will be stopped. If no more than two vaccine-related adverse events of grade  $\geq 3$  occur after the third DNA vaccination in each group, the combined immunization group will receive the rTV vaccine at the dose determined by the Phase Ia trial four weeks after the last DNA vaccination, while the DNA-only group will receive a placebo of the corresponding dose of the rTV vaccine. The placebo group will begin enrollment and vaccination at the same time as the low-dose subgroup of the combined immunization group and will receive placebos of the same volume as the DNA or rTV vaccines at the same time points. After the last vaccine or placebo administration, all participants will undergo at least six consecutive months of clinical and laboratory observation. In the Phase Ib trial, the interval between vaccinations in each group will be  $\geq 4$  weeks; if the time required for adverse reactions to heal or resolve exceeds 4 weeks, the interval between vaccinations will be  $\geq$  the actual time required for healing. The criteria for determining adverse events and their relationship to vaccination are detailed in Appendix 2 and Table 9.

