### (4) Immunogenicity Evaluation:

Immunogenicity evaluation will primarily be descriptive, reporting the positive rates of humoral and cellular immune responses.

For the Phase Ib study, differences in immunogenicity among different vaccination doses (combined immunization vs. DNA-alone), smallpox vaccination history, and study groups (vaccine vs. placebo) will be compared using logistic regression. The outcome variable (Y) will be the presence or absence of humoral/cellular immunity, with independent variables including vaccination dose (high vs. low), immunization strategy (combined vs. DNA-alone), smallpox vaccination history (vaccinated vs. unvaccinated), and study group (vaccine vs. placebo). For immune response intensity indicators such as antibody titers and Elispot counts, repeated measures ANOVA will be used. If the data do not meet the conditions for repeated measures ANOVA, appropriate data transformations will be applied.

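### Section 6.10.3 gives the randomisation no means of delivering the equal smallpox-history split that section 6.4.2 aims for in each combined-immunisation dose subgroup

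*Protocol*

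**What the plan says.** Section 6.4.2 of the protocol sets the sizes and the balance aim. It makes the two combined-immunisation dose subgroups 12 people each. On prior vaccination it then says: "Recruitment will aim to include an equal number of individuals who have and have not received the smallpox vaccine in each" of these two subgroups, which for 12 people means 6 and 6. The aim is not extended to the placebo or DNA-only groups.

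Section 6.10.3 sets the allocation. It states that "a block randomization method will be employed in this trial". On staging it adds: "The 36 participants will be divided into two phases based on the order of enrollment, with 18 participants in each phase". Each set of 18 is split 2:1, the earlier set between low-dose combined immunisation and placebo, the later set between high-dose combined immunisation and DNA alone. The section gives no block size, stratification factor or separate list. (I call the two enrolment phases stages below, to keep them apart from Phase Ib.)

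Section 6.4 defines prior smallpox vaccination by age, scar and vaccinia antibody. Section 6.3 places screening before the randomisation number, so history is known when a person is allocated. Section 6.10.5(4) uses history as an independent variable in the logistic regression for immunogenicity. The safety analysis in 6.10.5(3) has no history term.

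**The concern.** Blocking controls how many people enter each arm. It does not control which people. If the 18 in a stage are recruited at 9:9, chance still decides how they fall into the 12 and the 6.

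The protocol gives reasons to care about the factor:

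- Section 6.4.3 says people revaccinated with vaccinia have milder and shorter skin reactions. Annex 2 grades rTV site reactions mainly by diameter, and grade 3 or higher local reactions are a primary safety endpoint (6.2.1.1).
- The immunogenicity question in Table 3 compares the two DNA doses after the same rTV boost. The two dose subgroups are filled in successive stages and are not randomised against each other, so matching them on history is one of the few design safeguards for that comparison.
- Section 6.4 requires unvaccinated participants to be under 27, so an imbalance in history is largely an imbalance in age as well.

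At stake are the comparability of the two dose subgroups and the precision of the history comparison within arms of 12.

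**Working it through.** **Inputs from the protocol.** 18 per stage, two stages, 2:1 allocation (6.10.3); 12 per dose subgroup and the equal-number aim (6.4.2).

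**Assumption.** 9 experienced and 9 naive per stage. The protocol does not state this mix; it is the most favourable one, and others are shown below.

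**The plan's own figures.** 18 × 2/3 = 12 and 18 × 1/3 = 6; 2 × 18 = 36. These agree with 6.4.2.

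**Split of one stage.** The number x of experienced people among the 12 is hypergeometric: P(x) = C(9,x) × C(9,12−x) / C(18,12), with C(18,12) = 18,564.

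| Split in the 12 (either direction) | Ways | Probability | Left in the 6 |
|---|---|---|---|
| 6:6 | 84 × 84 = 7,056 | 38.0% | 3:3 |
| 7:5 | 2 × 36 × 126 = 9,072 | 48.9% | 2:4 |
| 8:4 | 2 × 9 × 126 = 2,268 | 12.2% | 1:5 |
| 9:3 | 2 × 1 × 84 = 168 | 0.9% | 0:6 |

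- Within 7:5: (7,056 + 9,072) / 18,564 = 86.9%.
- 8:4 or worse: (2,268 + 168) / 18,564 = 13.1%.
- 6:6 in both stages: 0.380² = 14.4%.
- 8:4 or worse in at least one stage: 1 − (1 − 0.131)² = 24.5%.

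**Low against high dose.** From the same distribution applied independently to both stages, the two dose subgroups differ in their number of experienced people in 72.9% of cases, and by two or more in 29.6%. If history shifts a response rate by δ, a difference of two shifts the unadjusted dose contrast by 2/12 × δ = δ/6.

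**Precision of a history contrast within one arm.** Its variance is proportional to 1/a + 1/b. Relative to 6:6, a 7:5 split gives (1/7 + 1/5) / (1/6 + 1/6) = 1.029, a rise of 2.9%. An 8:4 split gives (1/8 + 1/4) / (1/3) = 1.125, a rise of 12.5%.

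**Other mixes.** P(6:6) is 31.7% with 8:10 enrolled, 17.4% with 7:11 and 5.0% with 6:12. If the mix is left to chance at one half, it is C(12,6) / 2¹² = 924 / 4,096 = 22.6%.

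**Does blocking help?** With 9:9 in random enrolment order and blocks of 3, 6 or 9, P(6:6) stays near 38%. With strictly alternating enrolment it is 33.6%, 36.0% and 37.1% for those block sizes. If all of one history type enrol before the other, it rises to 60% with blocks of 6 and to 100% with blocks of 3 or 9. The protocol specifies no such order.

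**After the fix.** 9 × 2/3 = 6 from each stratum to the dose subgroup and 3 from each to the comparator: 6:6 and 3:3 with certainty.

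**The case against.** **Silence is not exclusion.** Section 6.10.3 names no stratum but does not rule one out, and section 5.3 leaves the randomisation process to the data management centre. A reader might infer that the list is unstratified; the document does not establish that. What stands is that the section which fixes method, ratio and order makes no provision for the balance that 6.4.2 asks for.

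**The equal split is an aim.** It is worded as something recruitment will try for, and it covers only the two dose subgroups. Counting every 7:5 as a failure overstates the matter, since about 87% of allocations are 6:6 or 7:5 and a 7:5 split costs little precision. This stands and limits the size of the point.

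**Confounding with the control arms.** A reader might infer that a 1:5 comparator would bias the safety comparison with placebo or DNA-only. The protocol does not support that for rTV skin reactions. Neither group receives rTV (6.4.2, Table 5), so prior vaccination cannot modify an rTV reaction in them. Section 6.10.4 expects reactions to rTV and placebo to be plainly different. The synopsis also reports no vaccine-related event of grade 3 or higher among the 12 Phase Ia subjects, who included people with and without prior vaccination.

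**The analysis already handles part of it.** Baseline comparisons are planned, and history is in the immunogenicity model. A measured, adjusted imbalance is mainly a loss of efficiency. Section 6.4.3 speaks of skin reactions and does not say that history changes the HIV-specific ELISPOT response. This stands for immunogenicity, although a four-variable logistic model in 36 people adjusts only weakly. It does not cover safety, where no adjustment is planned.

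**Conclusion.** The point holds as a mismatch between two sections: 6.4.2 sets a balance aim and 6.10.3 describes an allocation that does not provide for it. With 9:9 per stage, the exact split is reached in 38.0% of allocations per stage and 14.4% in both; 8:4 or worse occurs in 13.1% per stage and 24.5% in at least one. Any other mix lowers the chance of 6:6. The figures assume no unstated stratified list and no enrolment of one history type ahead of the other.

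The harm is mainly lost balance and precision in the low- versus high-dose comparison and in the smallpox-history comparison, for rTV local reactions and immunogenicity. No stated analysis becomes invalid. I would label this a cheap improvement.

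**What to change.** State in 6.10.3 that randomisation within each stage is stratified by smallpox-vaccination history as determined at screening, with enrolment capped at 9 per stratum and each stratum allocated 6:3. Use one permuted block of 9 per stratum, or undisclosed block sizes, because fixed blocks of 3 make the last assignment in each block easier to predict at a single site. Keep history as a factor in the analysis. If a stratified list already exists, 6.10.3 need only say so.

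The cost is a second list per stage and possible waiting for the slower stratum. The firm cap of 9 replaces what is now only an aim. No additional participants are needed.

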### **6.10.4 Blinding Design**

Given that this trial includes a combined immunization group, a DNA-only group, and a placebo group, a blinded design will be implemented to prevent subjective bias among researchers during vaccination, clinical observation, and laboratory testing. However, since the reactions of participants before and after receiving the rTV vaccine and placebo are noticeably different, the blinding will no longer be effective for participants and clinical observers (but will remain effective for laboratory personnel) 3 days after the rTV vaccination.

In this Phase Ib trial, participants will be vaccinated with either the investigational vaccine or placebo under a blinded protocol. On days 3–4 after the last vaccination in each group, the blinding will be lifted jointly by the statistician, the principal investigator of the clinical trial, and the sponsor.

The blinding process will be carried out by personnel unrelated to the study, with assistance from the statistician, based on the random number table. This includes the preparation of blinded trial materials and emergency code-break envelopes. Each participant will be assigned a unique sequential number, with a corresponding blinded randomization code. After packaging the trial materials, the blinding codes will be stored in duplicate at both the clinical trial site and the sponsor's office.

### **6.10.5 Statistical Analysis Content and Methods**

(1) Subject Enrollment and Trial Completion Status.

(2) Analysis of Baseline Data of Enrolled Subjects:

For the description of baseline characteristics, continuous variables will be calculated for mean, median, standard deviation, maximum, minimum, and interquartile range; categorical data will be calculated for frequency, percentage, cumulative frequency, and cumulative

percentage.

A comparative analysis of baseline data will be conducted for the combined immunization group, DNA-alone group, and placebo group in the Phase Ib study. For measurement indicators that meet parametric analysis conditions, methods such as analysis of variance (ANOVA), t-tests, and analysis of covariance (ANCOVA) will be primarily used. If parametric methods are not applicable, non-parametric statistical methods such as rank-sum tests will be employed; for categorical data, the chi-square ( $\chi^2$ ) test will be used. Given the small sample size of this study, Fisher's exact test will be applied when the chi-square test is not suitable.

### (3) Safety and Tolerability Evaluation:

Descriptive analysis will be used for safety evaluation, including vital signs (blood pressure, pulse, temperature, respiration), physical examinations, complete blood counts, blood biochemistry, and other laboratory tests at each follow-up period. Repeated measures ANOVA will be used for statistical comparison of measurement indicators across different follow-up periods. Electrocardiogram (ECG) results will list the status at each follow-up period and changes before and after the trial, along with a list of subjects with abnormal results.

Descriptive analysis will be performed for adverse events and adverse reactions (definitely related, possibly related, or indeterminable to vaccination) during the trial. For adverse events and reactions with higher incidence rates, the chi-square test will be used for statistical comparison; for those with very low incidence rates, statistical testing based on the Poisson distribution will be conducted.

Subjects included in the safety analysis must meet the following criteria:

- Meet all inclusion and exclusion criteria.
- Receive at least one dose of the vaccine.

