### 3. Adverse events following vaccination:

- If the participant exhibits the following symptoms within 2 hours after vaccination:
  - Respiratory symptoms: including chest tightness, palpitations, or difficulty breathing;
  - Circulatory failure symptoms: including pallor or cyanosis, bradycardia, weak or absent pulse, hypotension, or cold extremities;
  - Central nervous system symptoms: such as confusion, convulsions, or coma.
- If the participant experiences a grade 3 or higher systemic or local adverse event or laboratory abnormality related to vaccination.

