### 4. Inability to participate in follow-up or specimen collection:

- If a participant's repeated inability to attend follow-ups or provide specimens significantly impacts data collection, the sponsor and clinical trial unit may decide to terminate their participation early.

For participants who withdraw due to adverse events, the reason and date of termination must be recorded on the adverse event report form and reported within 24 hours to the Safety Supervision Department of the National Medical Products Administration (NMPA), the sponsor, and the Institutional Review Board (IRB). Whenever possible, follow-up should continue until the expected end of the trial, but at least until the adverse event stabilizes or resolves.

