#### **6.10.7 Treatment of Missing Values**

In statistical analysis, missing values will not be imputed. Unless otherwise specified, all results are based on data with available analytical values.

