#### **6.10.8 Statistical Analysis Software**

In this report, unless otherwise specified, all analysis results were generated using the licensed SAS 9.1.3 software. The software SITE number is: 47174001.

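### Repeated measures ANOVA without imputation can exclude any participant who misses one visit; a mixed model on all available visits would avoid this in arms of 12 and 6

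*Protocol*

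**What the plan says.** Section 6.10.5 (3) opens with descriptive analysis at each follow-up period, then fixes the test for continuous safety data: "Repeated measures ANOVA will be used for statistical comparison of measurement indicators across different follow-up periods". Section 6.10.5 (4) makes the immunogenicity evaluation mainly descriptive, with logistic regression for response rates, and adds: "For immune response intensity indicators such as antibody titers and Elispot counts, repeated measures ANOVA will be used". If that method's conditions fail, one remedy is offered: "If the data do not meet the conditions for repeated measures ANOVA, appropriate data transformations will be applied".

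On missing data, section 6.10.7 says "In statistical analysis, missing values will not be imputed", followed by "Unless otherwise specified, all results are based on data with available analytical values". Section 6.10.8 states that "all analysis results were generated using the licensed SAS 9.1.3 software" but names no procedure.

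Section 6.7.1 lists the circumstances in which a participant's study ends early. One of them reads: "If the participant experiences a grade 3 or higher systemic or local adverse event or laboratory abnormality related to vaccination". For participants withdrawn because of adverse events, the section adds: "Whenever possible, follow-up should continue until the expected end of the trial, but at least until the adverse event stabilizes or resolves".

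**The concern.** Classical repeated measures ANOVA is built on a full set of visits per participant. If a visit is missing and nothing is imputed, the complete-profile form omits the participant altogether, including the values that were measured. A data transformation does not restore a missing visit.

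Two things are at stake. First, the schedule is long and the arms are small, so scattered missed visits can remove a large part of an arm from the comparison of ELISPOT intensity. ELISPOT is the primary immunogenicity endpoint in section 6.2.1.2. Second, missingness can depend on the outcome. A participant withdrawn for a vaccine-related grade 3 or higher laboratory abnormality is assured of follow-up only until the event stabilises or resolves. If follow-up does end there, the profile is incomplete, and the formal laboratory comparison loses a participant with one of the largest changes.

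**Working it through.** The protocol states no power, effect size or dropout rate. Section 6.10.2 takes the 36 participants from a regulatory requirement. There is therefore no figure of the plan's own to reproduce. The arm sizes in section 6.4.2 do add up: 12 + 12 + 6 + 6 = 36.

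**Visit counts.**
- ELISPOT after the last vaccination: 7 visits (weeks 2, 4, 8, 12, 16, 20 and 24, section 6.2.1.2).
- ELISPOT over the whole trial: 13 time points in Table 6, which is 12 after the week 0 baseline.
- Routine blood test: 12 time points in Table 6, which is 11 after screening.

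**Formula.** If each visit is missed independently with probability m, the share of participants with all k visits is (1 − m)^k. The expected number complete in an arm of n is n(1 − m)^k. The values of m are assumptions, shown as a range.

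**Results.** Each cell gives the share complete, then the expected number complete of 12 and of 6.

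| Series | k | m = 2% | m = 5% | m = 10% |
|---|---|---|---|---|
| ELISPOT, after last vaccination | 7 | 0.868 (10.4; 5.2) | 0.698 (8.4; 4.2) | 0.478 (5.7; 2.9) |
| Routine blood test, post-baseline | 11 | 0.801 (9.6; 4.8) | 0.569 (6.8; 3.4) | 0.314 (3.8; 1.9) |
| ELISPOT, all post-baseline | 12 | 0.785 (9.4; 4.7) | 0.540 (6.5; 3.2) | 0.282 (3.4; 1.7) |

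For example, 0.95^7 = 0.698, and 12 × 0.698 = 8.4.

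**Check of the mechanism.** Data were simulated for 12 participants over 7 visits (84 values), and the last 3 visits of one participant were removed. A classical repeated measures ANOVA routine refused the data as unbalanced. Restricting to complete profiles leaves 11 participants and 11 × 7 = 77 values. A mixed model used all 12 participants and 84 − 3 = 81 values. The 4 values measured before that participant's gap are kept only by the mixed model.

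**The case against.** The strongest reply is that the protocol nowhere orders incomplete records to be deleted. Section 6.10.7 bases results on available values, and no SAS procedure is named. A univariate repeated measures ANOVA with participant as a factor, or a likelihood fit of the same model, can use partial records. This stands. A reader might infer that the plan drops every participant with a missed visit, but the text does not say so. What remains is that the method is named without qualification, its usual form needs complete profiles, and transformation is the only fallback.

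A reader might also infer that participants stopped for a grade 3 or higher laboratory abnormality fall out of the safety evaluation, or that the safety results as a whole are biased towards no change. The documents do not support this, for two reasons.
- Section 6.7.1 asks for follow-up to the expected end of the trial whenever possible; resolution of the event is the minimum. Section 6.5.8 describes the same trigger as stopping immunization, and Table 6 sets visits by week number. Such a participant may therefore still supply later values.
- The abnormal value is counted elsewhere: in the per-visit descriptive summaries (6.10.5 (3)), the abnormal change rates (6.10.1), the proportion with grade 3 or higher events (Table 3) and the primary safety endpoints (6.2.1.1).

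An example shows the limit. Suppose one of 12 participants has CK at 3.1 × ULN, the lower grade 3 bound in Annex 2, and the other 11 are assumed to be at 0.5 × ULN. The visit mean is (11 × 0.5 + 3.1)/12 = 0.72 × ULN. The descriptive summary would report 0.72. Only a complete-profile test that lost this participant would work from 0.50.

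Finally, the procedure and the covariance structure are ordinary content for an analysis plan. That is true, but here the protocol itself names the method and the missing-data rule, so their combination can be judged from the protocol.

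**Conclusion.** The point holds in a limited form. As written, the inferential comparisons of continuous laboratory and vital-sign values, and of titres and ELISPOT counts, can lose any participant with one missed visit. These may include some withdrawn for a vaccine-related grade 3 or higher abnormality whose follow-up ends at resolution. The primary safety endpoints, adverse event counts and descriptive summaries are untouched.

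The size depends on a missing-data rate that the documents do not give. For the 7 ELISPOT visits after the last vaccination, between 87% (2% missing per visit) and 48% (10%) of participants would be complete, with about 70% at 5%. These figures assume independent missed visits and a complete-profile analysis. They describe loss of participants only; they do not measure the bias from outcome-related withdrawal. The loss is avoidable by wording alone, so the change is worth making.

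**What to change.** In 6.10.5 (3) and (4), replace repeated measures ANOVA with a linear mixed model for repeated measures fitted by REML to all available visits. Use group, visit and group-by-visit as fixed effects, the baseline value as covariate, a parsimonious within-participant covariance and Kenward-Roger degrees of freedom. Analyse titres and spot counts on the log scale. State that no participant with at least one post-baseline value is excluded. Keep the no-imputation rule in 6.10.7.

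If each participant's maximum post-vaccination laboratory change is also reported, present it descriptively, with scheduled and unscheduled values shown separately. Note a to Table 6 adds repeat testing when CK is abnormal, so a maximum over all values would run higher in those tested more often.

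The cost is a few sentences. No further participants, visits or data are needed, and the model can be fitted in the SAS version already named. The small downside is that a covariance structure must be chosen and the model relies on data being missing at random. That assumption is weaker than the one behind analysing complete profiles only.

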**Table 3. Scientific problems to be solved by this phase Ib clinical trial**

| Problems                                                                                                                                                                                     | Primary safety endpoint events                                                                                                                            |
|-----------------------------------------------------------------------------------------------------------------------------------------------------------------------------------------------------|------------------------------------------------------------------------------------------------------------------------------------------------------------------|
| Is a single intramuscular injection of 2 mg or 4 mg of the DNA vaccine safe?                                                                                                                        | The proportion of participants experiencing grade 3 or higher adverse events within 4 weeks after the first vaccination in each group.                           |
| Is it safe to administer three consecutive intramuscular injections of 2 mg or 4 mg of the DNA vaccine?                                                                                             | The proportion of participants experiencing grade 3 or higher adverse events within 4 weeks after each vaccination in each group.                                |
| Is the combined vaccination regimen of three doses of the DNA vaccine at different doses followed by one dose of the replicating recombinant vaccinia virus vaccine safe?                           | The proportion of participants experiencing grade 3 or higher adverse events from the first vaccination until 24 weeks after the last vaccination in each group. |
|                                                                                                                                                                                                     | Primary immunogenicity endpoint events                                                                                                                    |

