#### **6.10.6 Hypothesis Testing and Significance**

All statistical tests will be conducted at a 5% significance level. P-values will be provided for all hypothesis tests.

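### At 12 versus 6, the prescribed chi-square and Poisson tests cannot show a vaccine excess over placebo for any related grade 3+ count that the halting rule permits after a DNA dose

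*Protocol*

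**What the plan says.** Table 3 (protocol section 4) puts the primary questions in the form "Is it safe to administer three consecutive intramuscular injections of 2 mg or 4 mg of the DNA vaccine" and attaches to each the proportion of participants with a grade 3 or higher adverse event in each group. The windows are four weeks after the first dose, four weeks after each dose, and from the first dose to 24 weeks after the last.

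Section 6.10.5 (3) starts from description: "Descriptive analysis will be performed for adverse events and adverse reactions". It then adds two tests: "For adverse events and reactions with higher incidence rates, the chi-square test will be used for statistical comparison", and "for those with very low incidence rates, statistical testing based on the Poisson distribution will be conducted". For measured safety variables it adds repeated measures ANOVA. Section 6.10.6 states: "All statistical tests will be conducted at a 5% significance level. P-values will be provided for all hypothesis tests". Fisher's exact test is named only in the baseline paragraph, 6.10.5 (2).

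Section 6.10.3 randomises 18 participants 2:1 to low-dose combined or placebo, then 18 participants 2:1 to high-dose combined or DNA-only. Section 6.4.2 lets the trial go on with at most two vaccine-related grade 3+ events after a DNA dose; for the low-dose subgroup, "if three or more such adverse events occur, subsequent vaccinations will be halted". Fever above 39°C lasting no more than 3 days is not counted in that subgroup.

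**The concern.** A between-group test at 5% can help answer a safety question only if some plausible result could reach significance. Here the Poisson test is assigned to very rare events and the group sizes are 12 and 6. The halting rule also keeps the related per-dose count at two or fewer in any cohort that goes on to the next dose. If no count in that range can give p<0.05 in the harmful direction, the p-value is settled in advance and carries no information about risk.

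At stake is how the primary objective is reported. A p-value near 1 beside a grade 3+ comparison is easily taken as reassurance, while the same data still allow a high true rate.

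**Working it through.** **Inputs.** Group sizes are 12 low-dose combined, 12 high-dose combined, 6 DNA-only and 6 placebo (6.4.2): 12+12+6+6=36, and 18 split 2:1 gives 12:6 twice (6.10.3). The level is 5% (6.10.6), taken as two-sided because sidedness is not stated. The most related grade 3+ events allowed after a DNA dose is two (6.4.2), with one event per participant assumed. Section 6.10.2 bases the 36 on a regulatory requirement and gives no power or event rate, so there is no planned figure to reproduce.

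**Chi-square at the limit.** For 2/12 v 0/6, Pearson χ² = N(ad−bc)²/(product of margins) = 18×(2×6−10×0)²/(12×6×2×16) = 2592/2304 = 1.125, p=0.289.

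**Poisson at the limit.** The protocol does not name the variant, so three were tried, with x events on vaccine and none on placebo.
- Exact conditional: given x events in total, the vaccine count is Binomial(x, 12/18). For x=2 the outcomes 2, 1 and 0 have probabilities 4/9, 4/9 and 1/9, so the two-sided p is 1.0.
- Score: statistic x/2 = 1.0, p=0.317.
- Likelihood ratio: 2x·ln(18/12) = 1.622, p=0.203.

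**Vaccine above placebo, all at the limit (two-sided p).** Section 6.4.2 can be read as limiting the 4 mg groups jointly or separately, so both readings are shown.

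| Contrast | Pearson | Yates | Fisher | Poisson exact | Score | LR |
|---|---|---|---|---|---|---|
| One combined subgroup, 2/12 v 0/6 | 0.29 | 0.79 | 0.53 | 1.00 | 0.32 | 0.20 |
| DNA-only, 2/6 v 0/6 | 0.12 | 0.44 | 0.45 | 0.50 | 0.16 | 0.096 |
| 4 mg groups jointly, 2/18 v 0/6 | 0.39 | 1.00 | 1.00 | 1.00 | 0.41 | 0.28 |
| All DNA recipients, 4/30 v 0/6 | 0.34 | 0.81 | 1.00 | 1.00 | 0.37 | 0.23 |
| All DNA recipients, 6/30 v 0/6 | 0.23 | 0.55 | 0.56 | 0.60 | 0.27 | 0.14 |

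No entry is below 0.05. Only the low-dose v placebo contrast in the first row is randomised.

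**Smallest significant count, 12 v 6, none on placebo.**
- Pearson: 5/12 gives p=0.063, 6/12 gives p=0.034.
- Likelihood-ratio Poisson: 4 events p=0.072, 5 events p=0.044.
- Score Poisson: 7 events p=0.061, 8 events p=0.0455.
- Exact conditional Poisson: 8 events p=0.059, 9 events p=0.034.

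Even the most liberal variant needs more than twice the permitted count.

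**Power with no halting, 12 v 6.** With assumed true rates of 30% v 1%, Pearson power is 11.1%; with 20% v 1% it is 1.8%. The chance of three or more affected among the 12 is 74.7% at 30% and 44.2% at 20%, so the halting count would react long before the test.

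**What the data would still allow.** The exact one-sided 95% upper bound for 0/n is 1−0.05^(1/n): 22.1% for 0/12, 11.7% for 0/24 and 9.5% for 0/30. For 2/12 it is the 0.95 quantile of Beta(3,10), 43.8%.

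**Where the limit fails.** Two DNA-only events with none in the combined group are also permitted. For 2/6 v 0/24, Pearson χ² = 30×(2×24)²/(6×24×2×28) = 8.571, p=0.0034; Yates gives 0.044, Fisher 15/435 = 0.0345, exact Poisson (6/30)² = 0.040. A three-group chi-square on 0/24, 2/6, 0/6 gives p=0.005.

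**The case against.** A reader might infer that every per-dose grade 3+ comparison is bound to be non-significant. The documents do not support that.
- The DNA-only v combined contrast can reach p<0.05 within the limit, as shown. It does not compare vaccine with placebo, however, and before the rTV dose the high-dose and DNA-only participants have received the same DNA dose.
- The halting count and the Table 3 endpoint differ. The rule counts vaccine-related events, omits short high fever at low dose, and is assessed there within two weeks of each dose. Table 3 counts all grade 3+ events over four weeks and cumulatively, and Annex 2 grades fever above 39.0°C as grade 3. Two affected participants after each of three doses could add up to 6/12 v 0/6 (Pearson p=0.034).
- Events after rTV are not limited by the two-event rule for DNA doses, and data that trigger a halt would still be analysed.

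A reader might also infer that the plan treats non-significance as proof of safety. It does not say so: the safety analysis is first of all descriptive, and the objective is to observe safety and tolerability. Low power is normal in a 36-person phase Ib trial that makes no power claim.

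It can further be said that confidence intervals are commonly left to the statistical analysis plan. That is right, and their absence is not the point. The point is that the protocol itself fixes tests and mandatory p-values that cannot respond in the range where they will mostly be used. The dependence on the Poisson variant also stands, which is why three thresholds are given; none falls within the permitted range.

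**Conclusion.** The point holds in a limited form. For vaccine-related grade 3+ events after a single DNA dose, in a cohort that the halting rule allows to continue, the prescribed tests cannot show a vaccine excess over placebo. The smallest p across the six test variants and all vaccine-over-placebo contrasts tried is 0.096; for the randomised 12 v 6 comparison it is 0.20. Outside that range the per-dose limit does not apply, but at 12 v 6 the same thresholds (6/12 by uncorrected chi-square; 5, 8 or 9 events by Poisson variant) still govern a comparison with zero events on placebo.

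This rests on two-sided testing and one event per participant. The 30%, 20% and 1% rates are illustrative and affect only the power figures. It is a cheap improvement to a stated method; it is not a defect that invalidates the trial.

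**What to change.** In 6.10.5 (3), for grade 3+ and other rare adverse events, make the inferential summary the exact (Clopper-Pearson) one-sided 95% upper bound on the proportion of participants affected. Report it per arm for each Table 3 window, and pooled over the 24 DNA+rTV and the 30 DNA recipients where the window applies. Pooling mixes the two DNA doses, so show it beside the per-arm bounds. Add exact confidence intervals for the difference within each randomised phase.

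Either drop the chi-square and Poisson p-values for these events or keep them labelled as descriptive, with the Poisson variant named. Amend 6.10.6 to match, and state that a non-significant comparison will not be used to conclude safety or similarity.

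The cost is analysis wording and a few table columns. Participants, visits, vaccination and the halting rule are untouched. The price is a less favourable statement: 0/12 would be reported as not excluding a rate of up to 22.1%.
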